### **Rationale:**

- 1) The Ophthalmology Department, who was expected to enroll patients with non-infectious uveitis did not engage in BELIEVE after all. In the period where The Department of Dermatology and Allergy Centre, OUH were engaged in enrollment of patients, there were too few patients with Hidradenitis Suppurativa initiating biological therapy.

2+3) We decided to broaden the inclusion criteria to increase the study population.

### *Enrollment period*

**Protocol:** Participant enrollment was expected to run from 1st of April 2017 to 31st of March 2019 or until a minimum of 100 patients with inflammatory bowel disease (CD and UC), 100 patients with RA, and 120 patients with axSpA, PsA, PsO, HS and niU were achieved.

**SAP:** The enrollment period was between 1st of September 2017 and 31st of March 2020.

**Rationale:** We extended the enrollment period with a year to increase the study population but did however not succeed to reach the planned sample size.

### *Primary endpoint*

**Protocol:** The disease specific primary endpoint for UC is a Mayo Clinic Index of 2 or less (with no individual subscore >1).

**SAP:** In cases, where a full Mayo Clinic Index is missing, we will accept a Partial Mayo Clinic Index, which is the Mayo Clinic Index without the endoscopic subscore. However, in these cases, the primary endpoint will be a Partial Mayo Clinic Index of 1 or less [22, 23].

**Rationale:** Some IBD patients refrained from repeated colonoscopies, hence hindering calculation of a full mayo score for UC patients.

### ***Timing of outcome assessment***

**Protocol:** Patients were examined at two time points; at baseline and 14-16 weeks after treatment initiation, where primary endpoints are evaluated.

**SAP:** Outcome assessment was scheduled to be 14-16 weeks after treatment initiation but a window of +/- 4 weeks are allowed.

**Rationale:** Taking the COVID-19 pandemic into account, we have decided to allow a window of +/- 4 weeks for outcome assessment at the follow-up visit in order to prevent a large number of missing outcomes.

## **4.3. Analysis populations**

The primary analysis will be conducted according to the Intention-to-Treat (ITT) principle [24]. We define the ITT population as all CID participants who have signed informed consent and answered the FFQ (which will define the group allocation [the proxy for 'randomization'] of the participants in analogy to randomized trials) regardless of their adherence otherwise to the study protocol. A *per-protocol* population will be defined as those who adhered to the biological treatment during the observation period and have complete data used for the analyses at the end of the study, and no major protocol violations.

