## 3. Study methods

### 3.1. Study design

BELIEVE is an observational multi-center cohort study with prospective enrollment of CD, UC, RA, axSpA, PsA and PsO patients initiating treatment with a biologic agent (or switching to another). Treatment with biologics was assigned to the patients independent of BELIEVE and their habitual diet. When a patient was found to be a candidate for initiation of biologic treatment or switching to another biologic agent, they were invited to participate in the study. Patients were examined at two time points; at baseline and 14-16 weeks after treatment initiation, according to Danish clinical standards. The examination program included questionnaires (including a Food Frequency Questionnaire at baseline), clinical assessment and sampling of blood, urine, feces and intestinal biopsies (the latter only for UC and CD). The inclusion period was between 1st of September 2017 and 31st of March 2020 with follow-up until end of July 2020. The following centers in Denmark participated in inclusion of patients to BELIEVE: Department of Hepatology and Gastroenterology, Aarhus University Hospital; Diagnostic Centre, Silkeborg Regional Hospital; Department of Gastroenterology, Herlev and Gentofte Hospital; Medical Department, Hospital Sønderjylland; Department of Gastroenterology, Hospital of South West Jutland; Department of Medical Gastroenterology, Department of Rheumatology and Department of Dermatology and Allergy Centre, Odense University Hospital.

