### **5.2. Eligibility**

#### **5.2.1. Inclusion criteria**

- Patients with a verified diagnosis of CD, UC, RA, axSpA, PsA, PsO, HS or niU
- Initiation of biological therapy

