### 5.3. Adherence and reasons for withdrawal

The number of patients adhering to the protocol, i.e., those who continued the biological treatment from baseline to the follow-up visit, will be accounted for in the flowchart. Likewise, the flowchart will also account for the number of patients deviating from the protocol, i.e., they did not initiate biologic treatment after all, they ended treatment due to either adverse events or lack of efficacy, or they withdrew their consent (fig. 1).

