## 6. Analysis

### 6.1. Outcome definitions, measurement and calculation

#### 6.1.1. Primary outcomes

The primary endpoint [2] is the proportion of patients with a clinical response to therapy 14-16 weeks after initiation of treatment with a biological agent. Thus, the primary outcome will be a composite depending on the disease specific definitions of clinical response, defined below:

- CD/Crohn's disease: clinical remission, defined as Harvey-Bradshaw Index (HBI) of 4 or less [25].
- UC/Ulcerative colitis: clinical remission, defined as Mayo Clinic Score of 2 or less (with no individual subscore of >1) [26-28].
- RA/Rheumatoid arthritis: clinical response, defined as at least a 20% improvement according to the criteria of the American College of Rheumatology (ACR20) [29, 30].
- AxSpA/Axial spondyloarthritis: clinical response, defined as at least a 20% improvement according to the Assessment of Spondyloarthritis International Society (ASAS20) [31, 32].
- PsA/Psoriatic arthritis: clinical response, defined as at least a 20% improvement according to the criteria of ACR20 [33].
- PsO/Psoriasis: clinical response, defined as at least a 75% improvement in the Psoriasis Area and Severity Index (PASI 75) [34].

For the measurement and calculation of HBI, Mayo Clinic Score and PASI see table A. ACR20 and ASAS20 are composite outcome measures defined below with composites further explained in table A.

ACR20 is a composite measure developed by the American College of Rheumatology for assessment of improvement of RA patients in clinical trials [30] but also used for assessment of PsA [33]. ACR20 is defined as  $\geq 20\%$  improvement in tender and swollen joint counts and  $\geq 20\%$  improvement in at least three out of the following five measures: 1) pain, 2) patient global assessment, 3) physician global assessment, 4) self-assessed

physical disability and 5) CRP or erythrocyte sedimentation rate. Information for calculation of ACR20 will be extracted from the Simplified Disease Activity Index (SDAI; patients and physicians global assessment and tender and swollen joint count) and the Health Assessment Questionnaire Disability Index (HAQ-DI; disability, see table A), while pain is a separate question in the self-administered questionnaire ("how much pain due to your arthritis do you suffer from, the past two days?") on a VAS 0-100 mm.

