#### 6.1.4. Exposure and confounding variables

##### **Exposure variable**

We will stratify the patients in BELIEVE into two groups (exposed versus unexposed) based on the ratio of fiber to meat intake (FtM [grams per day]):

$$FtM = \frac{\text{Fibers}}{\text{Red and processed meat}},$$

which will be calculated from the food frequency questionnaire (FFQ) administered to the patients at baseline. From this ratio, exposure is defined as the upper 33.3% of the total study sample (called the high fiber low meat group, HFLM) leaving the lower 66.6% of the sample as those un-exposed (low fiber high meat, LFHM).

Secondary explorative analysis will include defining exposure as 1) the upper 33.3% (high fiber; HF) of the study sample with respect to intake of dietary fibers (versus the lower 66.6% [low fiber; LF], and 2) the lower 33.3% (low meat; LM) of the study sample with regard to red/processed meat intake (versus the upper 66.6% [high meat; HM]).

The FFQ used in the present study was developed and validated in relation to the 2007-2008 Danish Health Examination Survey [47]. It was internet-based and administered to the participants prior to initiation of biological therapy with questions covering the habitual dietary intake during the past month. The FFQ contained information from 267 different food groups. For each item, frequency of consumption was evaluated by eight categories ranging from “newer/seldom” to “twice or more per day”. In order to quantify portion sizes for main meals and other main food items, a photographic food atlas consisting of different food and meal series was included at the end of the questionnaire. However, fixed portion sizes were used for some food items with more standardized portion sizes such as fruits. The actual weight in grams for each food item will be derived by multiplying the reported frequency of consumption with estimated portion sizes. Total energy intake and intake of different nutrients will be quantified using the Danish Food Composition Tables (National Food Institute, Technical University of Denmark, <https://frida.fooddata.dk/>).

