## 6.2. Analysis methods

The baseline characteristics of the participants (table 1) will be summarized for each dietary exposure profile (HFLM and LFHM) using descriptive statistics. Data will be presented as either means and standard deviations (SDs), or medians and interquartile ranges (IQRs) for continuous outcomes, and numbers and percentages for binary outcomes.

The primary outcome is the proportion of patients with a clinical response to therapy 14-16 weeks after treatment initiation. Response is defined for each CID (see section 6.1.1.). The number and proportion of participants who achieved treatment response will be summarized based on dietary profile (fig. 2 and table 2). We will investigate the association between dietary profile at baseline (HFLM and LFHM) and treatment response (yes/no) on the ITT population using logistic regression models. A simple (unadjusted) logistic regression model, an adjusted model (adjusted for type of CID, clinical center, age, sex, smoking) and a propensity adjusted model (further adjusted for propensity score) will be presented in table 2. The Odds ratio (OR) of achieving clinical response at week 14-16 for CID patients in HFLM group (the upper 33.3 % of the study population based on the ratio of fiber to meat intake) versus the LFHM group (the lower 66.6 %) will be reported along with the 95 % confidence interval (CI) and two-sided p-value (fig. 2 and table 2). We will also perform similar analyses on the key secondary outcome measures (see 6.1.2.), corresponding to our pre-specified key secondary objectives.

Secondary explorative analyses will include repeating the logistic regression models for treatment outcomes using secondary predictors of interest; 1) the upper 33.3% (high fiber; HF) vs. the lower 66.6% (low fiber; LF) of the study sample with respect to intake of dietary fibers (adjusted for meat intake), and 2) the lower 33.3% (low meat; LM) vs. the upper 66.6% (high meat; HM) of the study sample with regard to red/processed meat intake (adjusted for fiber intake). In addition, a possible interaction between the lower 33.3% of the sample

with respect to red/processed meat intake and the upper 33.3% of the sample with regard to fiber intake will be examined using logistic regression with same covariates as stated above.

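### The primary ITT set in section 4.3 keeps patients who never started a biologic, for whom the initiation-anchored endpoint is not defined; the expected effect on the primary odds ratio is small, but the population should be reconciled with sections 5.2.1 and 5.3

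*SAP*

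**What the plan says.** SAP section 4.3 makes consent and a completed questionnaire sufficient for the primary set: "We define the ITT population as all CID participants who have signed informed consent and answered the FFQ", and this applies "regardless of their adherence otherwise to the study protocol". Section 6.1.4 says the questionnaire was "administered to the participants prior to initiation of biological therapy". A patient can therefore qualify before any biologic is given.

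Section 5.3 lists, among the deviations to be counted in the flow chart, patients for whom "they did not initiate biologic treatment after all". No section takes them out of the primary set.

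Other sections tie the study to treatment start. Section 5.2.1 lists "Initiation of biological therapy" as an inclusion criterion. Section 2.3 directs the aim at patients who are starting a biologic. Section 6.1.1 defines the primary endpoint as "the proportion of patients with a clinical response to therapy 14-16 weeks after initiation of treatment with a biological agent".

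Section 6.2 models "treatment response (yes/no) on the ITT population using logistic regression models". Section 6.3 attempts follow-up of everyone who consented. Where a participant has an FFQ but no follow-up outcome, it multiply imputes the outcome under MAR.

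**The concern.** A patient who never starts has no initiation date, so neither the week 14-16 visit nor the window of 4 weeks either side can be placed. The SAP then handles this patient in four ways that do not agree with one another:

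- **Outcome missing:** the primary analysis imputes a treatment response from a model informed largely by treated patients.
- **Disease score observed:** the score would be used as it stands. The Crohn's disease and ulcerative colitis definitions are absolute thresholds (for example HBI of 4 or less), so an untreated patient below the threshold counts as a drug response.
- **Non-responder imputation (section 6.4):** never starting becomes drug failure when the outcome is missing.
- **Continuation of the biologic (key secondary outcome):** the answer is no, the same as for a patient who started and stopped.

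The diets of never-starters also enter the tertile cut-off, which section 6.1.4 takes on the whole study sample. What is at stake is mainly what the primary estimate describes, and after that how the sensitivity and continuation results are read.

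**Working it through.** **1. Do the planned analyses isolate the patients who started?** Against sections 4.3 and 6.4:

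- Primary (ITT with multiple imputation): never-starters are in.
- Complete case: they drop out only if their outcome is missing, and starters lost to follow-up drop out with them.
- Non-responder imputation: they are in, as failures if the outcome is missing.
- Per protocol: they are out, but so are starters who did not adhere, had incomplete data or had a major violation.
- Unmodified eligibility: this restricts drug class and previous biologic use, and does not require initiation.

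None of these is the set of all who started.

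**2. The plan's own figure.** Inputs from section 3.2: total 318 at 1:2 (106 and 212), response 60% and 40%, two-sided 0.05.

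- Pooled rate = (0.60 + 2 × 0.40)/3 = 0.4667.
- SE under the null = √[0.4667 × 0.5333 × (1/106 + 1/212)] = 0.0593.
- SE under the alternative = √[0.6 × 0.4/106 + 0.4 × 0.6/212] = 0.0583.
- Power = Φ[(0.20 − 1.96 × 0.0593)/0.0583] = 0.924.

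The stated 0.924 reproduces. The odds ratio at these rates is (0.6/0.4)/(0.4/0.6) = 2.25.

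**3. Primary analysis.** The SAP gives no never-starter share, so the shares here and below are assumptions. With the same share f in both groups and all their outcomes missing, the average number imputed as responders is 106 × f × 0.6 + 212 × f × 0.4:

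- f = 5%: about 16 never-starters, 7.4 imputed responders.
- f = 10%: about 32 never-starters, 14.8 imputed responders.

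These are counts of draws, and they do not measure bias. A simulation used 10% never-starters in HFLM and 5% in LFHM, all outcomes missing, five imputations, and diet group as the only predictor. It gave an average odds ratio of 2.25 in starters only and 2.24 after imputation, with mean standard errors of 0.255 and 0.257. Auxiliary variables could move this somewhat.

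**4. Non-responder imputation, equal shares.** Each response rate is multiplied by (1 − f).

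- f = 5%: 57% and 38%, OR = (0.57/0.43)/(0.38/0.62) = 2.16.
- f = 10%: 54% and 36%, OR = (0.54/0.46)/(0.36/0.64) = 2.09.

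**5. Non-responder imputation, unequal shares.**

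- Starters at 60% and 40%, never-starters 10% in HFLM and 5% in LFHM: 54% and 38%, OR = (0.54/0.46)/(0.38/0.62) = 1.92.
- The reverse (5% and 10%): 57% and 36%, OR = (0.57/0.43)/(0.36/0.64) = 2.36.
- No diet effect among starters (46.7% in both groups): 0% against 10% gives OR 1.21, and 10% against 0% gives OR 0.83.

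**6. Cost of restricting to starters.** The formula in step 2 with 106(1 − f) and 212(1 − f):

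- f = 5%: power 0.911.
- f = 10%: power 0.896.

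**The case against.** The SAP openly chooses analysis by baseline diet group whatever happens to treatment, shows never-starters in the flow chart, and plans sensitivity analyses that treat them differently. A reader might infer that the primary odds ratio is materially biased because drug responses are invented for people who took no drug. The documents do not support that, for three reasons:

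- Section 6.3 attempts follow-up of all who consented, so not every never-starter outcome is missing.
- Where it is missing, MAR imputation roughly returns the starters-only result (step 3).
- The larger shifts in step 5 belong to a sensitivity analysis and need both an assumed share and an assumed imbalance.

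It can also be argued that section 5.2.1 already makes never-starters ineligible. Section 5.3, however, treats them as enrolled patients who deviate, and section 4.3 sets no start condition, so the text does not settle it.

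The last argument is that requiring initiation conditions on an event after diet was recorded. This stands. Section 3.1 says that "Treatment with biologics was assigned to the patients independent of BELIEVE and their habitual diet", but that describes how treatment was assigned, not why a patient later failed to start. It does not show that exclusion is neutral. On the other side, diet was not randomised, so the restriction breaks no randomised comparison.

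**Conclusion.** The point holds as a mismatch between the primary population and the SAP's own inclusion criterion, aim and endpoint. The endpoint lacks a time anchor for never-starters however few they are, and no planned analysis covers exactly the patients who started.

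The numerical consequence is probably modest. No stated figure is wrong because of it, and material bias in the primary odds ratio is not shown. Under non-responder imputation with equal shares, 2.25 moves to about 2.16 at 5% and 2.09 at 10%. Unequal shares could bias it in either direction. All of this rests on assumed shares, the planned 318 patients (recruitment ended before 320) and the planned 60% and 40%. The effect on the tertile cut-off cannot be sized from the SAP. The change is worth making because it is cheap and brings the estimate into line with the stated question.

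**What to change.** Reconcile section 4.3 with sections 5.2.1 and 5.3:

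- Define the primary population as participants who consented, answered the FFQ and initiated the biologic, analysed by baseline diet group regardless of later adherence.
- Compute the fiber-to-meat, fiber and meat tertile cut-offs in that set.
- Report never-starters by diet group in Figure 1.
- Keep the set of all who consented and answered the FFQ as a sensitivity analysis, and state there how the assessment date is fixed for a patient with no initiation date.

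The cost is a change of wording, which section 2.1 places before database closure. No new data are needed, because section 5.3 already counts never-starters for the flow chart. The downsides are a slightly smaller sample, with the power given in step 6, and conditioning on treatment start. The by-group count and the retained sensitivity analysis make that conditioning visible.

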### 6.1.2. Key secondary outcome measures

Predefined key secondary outcomes include changes in generic outcomes from baseline to follow-up (14-16 weeks after treatment initiation) consisting of both clinical and patient reported outcomes (PRO):

- Health-related quality of life (HRQoL): the physical component summary from the Short Form Health Survey (SF-12 PCS)
- HRQoL: the mental component summary measure from the SF-12 (SF-12 MCS)
- HRQoL: symptom burden (from the short health scale [SHS])
- HRQoL (Disability): functional status (SHS)
- HRQoL: disease-related burden (SHS)
- HRQoL: general well-being (SHS)
- Acute phase reactant (CRP)
- Physician global assessment (0-100 mm VAS)
- Patient global assessment (0-100 mm VAS)

In addition, however not specifically defined in the published protocol:

- The proportion of patients continuing the biologic treatment (yes/no) at week 14-16.

The 12-item SF-12 is a shorter form of the Short Form 36 (SF-36) which is widely used for measuring HRQoL and has a range of 0-100 (higher values indicate better health), mean of 50 and a standard deviation of 10. The SF-12 questionnaire comprises questions about physical and social functioning over the past 4 weeks. From the SF-12, two summary measures can be estimated; PCS and MCS [35].

The Short Health Scale (SHS) is a four-item questionnaire assessing the patient's subjective experience of how their disease influences four health dimensions: 1) symptom burden (severity of symptoms, 0 = none, 100 = worst thinkable), 2) functional status (impact on daily activities, 0 = none, 100 = severely impaired function), 3) disease-related burden (concern over illness, 0 = none, 100 = constantly) and 4) general well-being (0 = good, 100 = terrible) [36]. The four questions are graded from 0-100 and presented individually, where higher

scores indicate negative experience. The SHS has been validated as a measure for HRQoL for use in UC [36] and CD [37].

CRP: Blood samples as specified in the protocol were collected by a trained laboratory technician and handled according to set procedures. Results from analysis of blood samples will be limited to CRP (mg/L) in this study.

Physician global assessment and patient global assessment\* is assessed on 100 mm VAS.

\* Patient global assessment is not collected for PsO, CD and UC.

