## 6.4. Sensitivity analyses

Where complete cases and multiple imputation analyses give different results, the analyst should attempt to understand why, and this should be reported in publications [52]. Robustness is a concept that refers to the sensitivity of the overall conclusions to various limitations of the data, assumptions, and analytic approaches to data analysis. Robustness implies that the treatment effect and primary conclusions of the trial are not

substantially affected when analyses are carried out based on alternative assumptions or analytic approaches. For the purpose of sensitivity, multiple sensitivity analyses will be performed to assess the robustness of the primary analyses. For instance, a simplistic 'single step, null responder imputation' would represent a conservative base case and is potentially valid even if data is 'missing not at random' as it assumes and implies that patients have not improved or worsened after entering the study. When there are missing outcome data for our dichotomous outcomes we will explore "best" and "worst" case scenarios by replacing missing values with "good" outcomes in one group and "bad" outcomes in the other group. Sensitivity analyses will include analyses based on:

- 1) complete case analysis,
- 2) a 'non-responder-imputation',
- 3) the 'per protocol population',
- 4) the population meeting the unmodified eligibility criteria  
(exclusion of patients initiating treatment with biologics targeting other agents than TNF and patients previously treated with biologics).

Results of the sensitivity analyses are presented in the Appendix, table 2. When the different sensitivity analyses are in agreement, and the analyses on the sensitivity analyses and the main analysis lead to essentially the same conclusions, confidence in the trial results is increased.

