Appendix Table 2. Sensitivity analyses of the comparison of HFLM versus LFHM.

| Outcome                                                                                                                                                                                                                                                                                                                                                                                                                                                                                                                                                | Complete-case analysis |      |                     | Non-responder imputation analyses |                     |          | Per protocol population |          |                     | Unmodified eligibility criteria |                     |          |
|--------------------------------------------------------------------------------------------------------------------------------------------------------------------------------------------------------------------------------------------------------------------------------------------------------------------------------------------------------------------------------------------------------------------------------------------------------------------------------------------------------------------------------------------------------|------------------------|------|---------------------|-----------------------------------|---------------------|----------|-------------------------|----------|---------------------|---------------------------------|---------------------|----------|
|                                                                                                                                                                                                                                                                                                                                                                                                                                                                                                                                                        | HFLM                   | LFHM | Difference (95% CI) | P value*                          | Difference (95% CI) | P value* | Difference (95% CI)     | P value* | Difference (95% CI) | P value*                        | Difference (95% CI) | P value* |

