| ΔPatient global assessment (0-100 mm VAS)                                                                                                                                                                                                                                                                                                                                                                                                                                                                                                              |                        |      |                     | n.a.                              |                     | n.a.     |                         | n.a.     |                     | n.a.                            |                     | n.a.     |
| Continuation of treatment, n (%)                                                                                                                                                                                                                                                                                                                                                                                                                                                                                                                       |                        |      |                     |                                   |                     |          |                         |          |                     |                                 |                     |          |
| Safety/Harms:                                                                                                                                                                                                                                                                                                                                                                                                                                                                                                                                   |                        |      |                     |                                   |                     |          |                         |          |                     |                                 |                     |          |

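### The per-protocol set keeps only patients who stayed on the biologic, so its continuation comparison is 100% vs 100% and its response comparison conditions on a post-baseline event tied to the outcome

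*SAP*

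**What the plan says.** Section 4.3 makes the ITT population primary. It defines the per-protocol set as "those who adhered to the biological treatment during the observation period and have complete data used for the analyses", with no major protocol violations.

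Section 5.3 says what adherence means: adherent patients are "those who continued the biological treatment from baseline to the follow-up visit". Among the ways of deviating from the protocol it lists that "they ended treatment due to either adverse events or lack of efficacy".

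Section 6.1.2 adds a key secondary outcome: "The proportion of patients continuing the biologic treatment (yes/no) at week 14-16".

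Section 6.4 lists the per-protocol analysis third of four numbered sensitivity analyses. It says that when these agree with each other and with the main analysis, "confidence in the trial results is increased".

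Appendix Table 2 has a column group headed "Per protocol population" and a row "Continuation of treatment, n" (%). The cells of that row are open. The patient global assessment row just above it and the Safety/Harms rows below it carry n.a. entries. The table footnote applies a multiplicity procedure to the key secondary outcomes.

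**The concern.** Membership of the per-protocol set requires a yes on one of the study's own outcomes, which raises two problems.

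- **Continuation cannot be compared in this set.** Everyone in it continued, so the planned comparison has no variation in the outcome. The multiplicity procedure in that column also receives no valid P value from this row. If the row were entered with P = 1, it would take first place in the ordering that section 4.1 describes, and the next P value would be judged at 0.05/2 instead of 0.05.
- **The response analysis is selected on something close to its outcome.** Stopping for lack of efficacy happens after baseline, is closely tied to non-response, and may itself depend on diet. Removing these patients can move the response odds ratio. Section 6.4 would read agreement between this analysis and ITT as support for the conclusion, and nothing in the plan warns that the set is selected in this way.

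**Working it through.** **The plan's own figure.** Section 3.2 gives power 0.924 for 60% vs 40% response, total N 318, ratio 1:2, two-sided 0.05. With 106 vs 212 patients and the pooled-variance normal approximation to Pearson's chi-square, the result is 0.9245. The figure reproduces and is not in dispute. The 60% and 40% are reused below.

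**Continuation.** No assumption is needed.

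- Section 4.3 with section 5.3: in the per-protocol set means continued the biologic to follow-up.
- Section 6.1.2: the outcome is continued, yes or no.
- For any true continuation rates, the per-protocol rates are therefore 100% and 100%. The difference is 0 by construction and the odds ratio is undefined.

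**Response.** Let r be the true response rate in a group and f the share of its non-responders who stop for lack of efficacy and are dropped. The SAP gives no f, so every value here is an assumption, as is treating every such patient as a non-responder.

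- Per-protocol response rate = r / (r + (1 − r)(1 − f)).
- The per-protocol odds are r / ((1 − r)(1 − f)), so per-protocol OR = true OR × (1 − f for LFHM) / (1 − f for HFLM).
- True OR at 60% vs 40% = (0.6/0.4) / (0.4/0.6) = 2.25.

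| f, HFLM | f, LFHM | Per-protocol rates (true 60% / 40%) | OR (true 2.25) | OR (true 1.00, 50% / 50%) |
|---|---|---|---|---|
| 10% | 10% | 62.5% / 42.6% | 2.25 | 1.00 |
| 50% | 50% | 75.0% / 57.1% | 2.25 | 1.00 |
| 10% | 30% | 62.5% / 48.8% | 1.75 | 0.78 |
| 30% | 10% | 68.2% / 42.6% | 2.89 | 1.29 |
| 10% | 50% | 62.5% / 57.1% | 1.25 | 0.56 |
| 50% | 10% | 75.0% / 42.6% | 4.05 | 1.80 |

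Worked row (10% / 30%): HFLM 0.6/(0.6 + 0.4 × 0.9) = 0.6/0.96 = 62.5%. LFHM 0.4/(0.4 + 0.6 × 0.7) = 0.4/0.82 = 48.8%. OR = 2.25 × 0.7/0.9 = 1.75.

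**Fewer early failures in one group are not enough to bias the odds ratio.** Suppose 10% of all HFLM patients and 15% of all LFHM patients stop for lack of efficacy. As shares of non-responders these are 10/40 = 25% and 15/60 = 25%. The rates become 60/90 = 66.7% and 40/85 = 47.1%, and the OR is (60/30)/(40/45) = 2.25, unchanged.

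**The case against.** The strongest reply has four parts.

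- **The set is secondary.** The primary analysis is ITT, regardless of adherence. The per-protocol set stands beside complete-case, non-responder-imputation and unmodified-eligibility analyses, plus best- and worst-case scenarios. This stands: the primary result is untouched, and 6.4 gives the per-protocol set no decisive role. It is nevertheless one of four numbered analyses whose agreement is to count as support.
- **An on-treatment set is a conventional contrast to ITT.** This also stands. The set may be kept, provided that the plan says what it conditions on.
- **Appendix Table 2 is an empty shell**, so an open cell is weak evidence of intent. This has some force, but neighbouring rows are marked n.a. and this one is not, and no text exempts it.
- **The selection need not bias the odds ratio.** Correct, as the equal-share rows show.

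A reader might go further in three ways that the document does not support. One could infer that the set must weaken or erase a diet effect; the bias needs unequal stopping shares and can run in either direction. One could infer that all stoppers are non-responders; section 5.3 also lists adverse-event stops, which may include responders, and section 6.1.1 does not define stopping as non-response. One could read section 6.1.4 as forbidding this restriction because it rules out descendants of the exposure; that rule selects confounders for the propensity score and does not govern analysis sets.

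**Conclusion.** The point holds, with limited reach. The continuation comparison in the per-protocol column is degenerate by definition, whatever the data. The response comparison in that set conditions on post-baseline stopping tied to the outcome. Response rates rise in any group where non-responders stop for lack of efficacy, but the odds ratio moves only when the stopping share differs by diet group.

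Under assumed shares of 10% and 30%, a true odds ratio of 2.25 becomes 1.75 or 2.89 depending on which group stops more, and a true odds ratio of 1.00 becomes 0.78 or 1.29. These sizes are illustrations, not estimates. Equal stopping cannot be taken for granted, because a difference in continuation between diet groups is among the things the study sets out to test. Agreement between this set and ITT is therefore not, by itself, evidence of robustness.

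**What to change.** 1. In Appendix Table 2, mark continuation of treatment n.a. in the per-protocol columns and leave it out of the multiplicity procedure for that column.
2. Choose one of these for the binary response outcome:
   - In section 4.3, keep patients who stopped for lack of efficacy in the set and count them as non-responders.
   - Leave the set on-treatment, and state in section 6.4 that it conditions on post-baseline stopping and that its agreement with the ITT result is not evidence of robustness.

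The cost is SAP wording and, under the first option, a changed population flag. No new data are needed: section 6.3 already plans follow-up of consenting participants who leave treatment. Under the first option the set is less strictly on-treatment, and a patient who stopped for lack of efficacy but met the response definition at follow-up would be counted as a non-responder, so the rule should be written out. That option covers only the binary response. If the continuous key secondary outcomes stay on-treatment in this set, the statement in section 6.4 is needed for them too.
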